**Modified MRC (mMRC) Dyspnoea Score**

## Modified MRC Dyspnoea Score

| Grade |                                                                                                                                               |  |
|-------|-----------------------------------------------------------------------------------------------------------------------------------------------|--|
| 0     | I only get breathless with strenuous exercise.                                                                                                |  |
| 1     | I get short of breath when hurrying on level ground or walking up a slight hill.                                                              |  |
| 2     | On level ground, I walk slower than people of the same age because of breathlessness, or have to stop for breath when walking at my own pace. |  |
| 3     | I stop for breath after walking about 100 yards or after a few minutes on level ground.                                                       |  |
| 4     | I am too breathless to leave the house or I am breathless when dressing.                                                                      |  |

**Hospital Anxiety and Depression Test**

Patient Name:  
ID Number:  
Date:

**HAD Scale**

This questionnaire is designed to help us know how you feel. Read each item and place a firm tick in the box opposite the reply, which comes closest to how you have been feeling in the past week.

Don't take too long over your replies; your immediate reaction to each item will probably be more accurate than a long thought-out response.

**Tick one box only in each section**

|                                                                                       |                          |                                                                                |                          |
|---------------------------------------------------------------------------------------|--------------------------|--------------------------------------------------------------------------------|--------------------------|
| 1 I feel tense or wound up:                                                    |                          | 8 I feel as if I am slowed down:                                        |                          |
| Most of the time (3)                                                                  |  | Nearly all the time (3)                                                        |  |
| A lot of the time (2)                                                                 |  | Very often (2)                                                                 |  |
| Time to time, occasionally (1)                                                        |  | Sometimes (1)                                                                  |  |
| Not at all (0)                                                                        |  | Not at all (0)                                                                 |  |
| 2 I still enjoy the things I used to enjoy:                                    |                          | 9 I get a sort of frightened feeling like "butterflies" in the stomach: |                          |
| Definitely as much (0)                                                                |  | Not at all (0)                                                                 |  |
| Not quite so much (1)                                                                 |  | Occasionally (1)                                                               |  |
| Only a little (2)                                                                     |  | Quite often (2)                                                                |  |
| Hardly at all (3)                                                                     |  | Very often (3)                                                                 |  |
| 3 I get a sort of frightened feeling as if something awful is about to happen: |                          | 10 I have lost interest in my appearance:                               |                          |
| Very definitely and quite badly (3)                                                   |  | Definitely (3)                                                                 |  |
| Yes, but not too badly (2)                                                            |  | I don't take so much care as I should (2)                                      |  |
| A little, but it doesn't worry me (1)                                                 |  | I may not take quite as much care (1)                                          |  |
| Not at all (0)                                                                        |  | I take just as much care as ever (0)                                           |  |
| 4 I can laugh and see the funny side of things:                                |                          | 11 I feel restless as if I have to be on the move:                      |                          |
| As much as I always could (0)                                                         |  | Very much indeed (3)                                                           |  |
| Not quite so much now (1)                                                             |  | Quite a lot (2)                                                                |  |
| Definitely not so much now (2)                                                        |  | Not very much (1)                                                              |  |
| Not at all (3)                                                                        |  | Not at all (0)                                                                 |  |
| 5 Worrying thoughts go through my mind:                                        |                          | 12 I look forward with enjoyment to things:                             |                          |
| A great deal of the time (3)                                                          |  | As much as I ever did (0)                                                      |  |
| A lot of the time (2)                                                                 |  | Rather less than I used to (1)                                                 |  |
| From time to time but not too often (1)                                               |  | Definitely less than I used to (2)                                             |  |
| Only occasionally (0)                                                                 |  | Hardly at all (3)                                                              |  |
| 6 I feel cheerful:                                                             |                          | 13 I get sudden feelings of panic:                                      |                          |
| Not at all (3)                                                                        |  | Very often indeed (3)                                                          |  |
| Not often (2)                                                                         |  | Quite often (2)                                                                |  |
| Sometimes (1)                                                                         |  | Not very often (1)                                                             |  |
| Most of the time (0)                                                                  |  | Not at all (0)                                                                 |  |
| 7 I can sit at ease and feel relaxed:                                          |                          | 14 I can enjoy a good book or radio or TV programme:                    |                          |
| Definitely (0)                                                                        |  | Often (0)                                                                      |  |
| Usually (1)                                                                           |  | Sometimes (1)                                                                  |  |
| Not often (2)                                                                         |  | Not often (2)                                                                  |  |
| Not at all (3)                                                                        |  | Very seldom (3)                                                                |  |

ANXIETY SCORE

DEPRESSION SCORE

## **Patient Activation Measurement (PAM)**

Below are some statements that people sometimes make when they talk about their health. Please indicate how much you agree or disagree with each statement as it applies to you personally by circling your answer. Your answers should be what is true for you and not just what you think others want you to say.

If the statement does not apply to you, circle N/A.

|                                                                                                                            |                   |          |       |                |     |
|----------------------------------------------------------------------------------------------------------------------------|-------------------|----------|-------|----------------|-----|
| 1. When all is said and done, I am the person who is responsible for taking care of my health                              | Disagree Strongly | Disagree | Agree | Agree Strongly | N/A |
| 2. Taking an active role in my own health care is the most important thing that affects my health                          | Disagree Strongly | Disagree | Agree | Agree Strongly | N/A |
| 3. I am confident I can help prevent or reduce problems associated with my health                                          | Disagree Strongly | Disagree | Agree | Agree Strongly | N/A |
| 4. I know what each of my prescribed medications do                                                                        | Disagree Strongly | Disagree | Agree | Agree Strongly | N/A |
| 5. I am confident that I can tell whether I need to go to the doctor or whether I can take care of a health problem myself | Disagree Strongly | Disagree | Agree | Agree Strongly | N/A |
| 6. I am confident that I can tell a doctor concerns I have even when he or she does not ask                                | Disagree Strongly | Disagree | Agree | Agree Strongly | N/A |
| 7. I am confident that I can follow through on medical treatments I may need to do at home                                 | Disagree Strongly | Disagree | Agree | Agree Strongly | N/A |
| 8. I understand my health problems and what causes them                                                                    | Disagree Strongly | Disagree | Agree | Agree Strongly | N/A |
| 9. I know what treatments are available for my health problems                                                             | Disagree Strongly | Disagree | Agree | Agree Strongly | N/A |
| 10. I have been able to maintain (keep up with) lifestyle changes, like eating right or exercising                         | Disagree Strongly | Disagree | Agree | Agree Strongly | N/A |
| 11. I know how to prevent problems with my health                                                                          | Disagree Strongly | Disagree | Agree | Agree Strongly | N/A |
| 12. I am confident I can figure out solutions when new problems arise with my health                                       | Disagree Strongly | Disagree | Agree | Agree Strongly | N/A |
| 13. I am confident that I can maintain lifestyle changes, like eating right and exercising, even during times of stress    | Disagree Strongly | Disagree | Agree | Agree Strongly | N/A |

Insignia Health. "Patient Activation Measure; Copyright © 2003-2011, University of Oregon. All Rights reserved." Contact Insignia Health at [www.insigniahealth.com](http://www.insigniahealth.com)

Insignia Health, LLC ☐ Proprietary and Confidential ☐ © 2011 ☐ For use with a valid copyright license only

**Work Productivity Activity Impairment Questionnaire****Work Productivity and Activity Impairment Questionnaire:  
General Health V2.0 (WPAI:GH)**

The following questions ask about the effect of your health problems on your ability to work and perform regular activities. By health problems we mean any physical or emotional problem or symptom. *Please fill in the blanks or circle a number, as indicated.*

1. Are you currently employed (working for pay)?      \_\_\_\_ NO      \_\_\_\_ YES  
*If NO, check "NO" and skip to question 6.*

The next questions are about the **past seven days**, not including today.

2. During the past seven days, how many hours did you miss from work because of your COPD? *Include hours you missed on sick days, times you went in late, left early, etc., because of your health problems. Do not include time you missed to participate in this study.*

\_\_\_\_ HOURS

3. During the past seven days, how many hours did you miss from work because of any other reason, such as vacation, holidays, time off to participate in this study?

\_\_\_\_ HOURS

4. During the past seven days, how many hours did you actually work?

\_\_\_\_ HOURS *(If "0", skip to question 6.)*

5. During the past seven days, how much did your COPD affect your productivity while you were working?

*Think about days you were limited in the amount or kind of work you could do, days you accomplished less than you would like, or days you could not do your work as carefully as usual. If health problems affected your work only a little, choose a low number. Choose a high number if health problems affected your work a great deal.*

Consider only how much COPD affected productivity while you were working.

|                                          |   |   |   |   |   |   |   |   |   |   |    |                                                      |
|------------------------------------------|---|---|---|---|---|---|---|---|---|---|----|------------------------------------------------------|
| Health problems had no effect on my work | 0 | 1 | 2 | 3 | 4 | 5 | 6 | 7 | 8 | 9 | 10 | Health problems completely prevented me from working |
|------------------------------------------|---|---|---|---|---|---|---|---|---|---|----|------------------------------------------------------|

CIRCLE A NUMBER

6. During the past seven days, how much did your COPD affect your ability to do your regular daily activities, other than work at a job?

*By regular activities, we mean the usual activities you do, such as work around the house, shopping, childcare, exercising, studying, etc. Think about times you were limited in the amount or kind of activities you could do and times you accomplished less than you would like. If health problems affected your activities only a little, choose a low number. Choose a high number if health problems affected your activities a great deal.*

Consider only how much COPD affected your ability to do your regular daily activities, other than work at a job.

|                                                      |   |   |   |   |   |   |   |   |   |   |    |                                                                        |
|------------------------------------------------------|---|---|---|---|---|---|---|---|---|---|----|------------------------------------------------------------------------|
| Health problems had no effect on my daily activities | 0 | 1 | 2 | 3 | 4 | 5 | 6 | 7 | 8 | 9 | 10 | Health problems completely prevented me from doing my daily activities |
|------------------------------------------------------|---|---|---|---|---|---|---|---|---|---|----|------------------------------------------------------------------------|

CIRCLE A NUMBER

**Veterans Specific Activity Questionnaire (VSAQ)**[figure not shown]

The following is a list of activities that increase in difficulty as you read down the page. Think carefully, then underline the first activity that, if you performed it for a period of time, would typically cause fatigue, shortness of breath, chest discomfort, or otherwise cause you to want to stop. If you do not normally perform a particular activity, try to imagine what it would be like if you did.

- |         |                                                                                                                                                               |
|---------|---------------------------------------------------------------------------------------------------------------------------------------------------------------|
| 1 METs  | Eating, getting dressed, working at a desk                                                                                                                    |
| 2 METs  | Taking a shower, shopping, cooking, walking down 8 steps                                                                                                      |
| 3 METs  | Walking slowly on a flat surface for 1 or 2 blocks, a moderate amount of work around the house, such as vacuuming, sweeping the floors, or carrying groceries |
| 4 METs  | Light garden work (ie, raking leaves, weeding, sweeping, or pushing a power mower), painting, or light carpentry                                              |
| 5 METs  | Walking briskly, social dancing, washing the car                                                                                                              |
| 6 METs  | Play 9 holes of golf carrying your own clubs. Heavy carpentry, mow lawn with push mower                                                                       |
| 7 METs  | Carrying 60 pounds, perform heavy outdoor work (ie, digging, spading soil, etc), walking uphill                                                               |
| 8 METs  | Carrying groceries upstairs, move heavy furniture, jog slowly on flat surface, climb stairs quickly                                                           |
| 9 METs  | Cycling at a moderate pace, sawing wood, skipping (slowly)                                                                                                    |
| 10 METs | Brisk swimming, cycling up a hill, jog 6 miles per hour                                                                                                       |
| 11 METs | Carry a heavy load (ie, a child or firewood) up 2 flights of stairs, cross-country ski, bicycling briskly, continuously                                       |
| 12 METs | Running briskly, continuously (level ground, 8 min per mile)                                                                                                  |
| 13 METs | Any competitive activity, including those that involve intermittent sprinting, running competitively, rowing competitively, bicycle riding                    |

[figure not shown]

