**Intervention effectiveness outcomes**

- The time to a two-point improvement in the COPD Assessment Tool (CAT) Score
- The improvement in CAT score at study completion 90(+/- 7) days in the MyCOPD support population compared to usual care
- The number of critical errors by inhaler at study completion 90(+/- 7)
- St Georges Respiratory Questionnaire (SGRQ) score at study completion 90(+/- 7)
- Modified MRC dyspnoea score at study completion 90(+/- 7)
- Patient Activation Measure (PAMs) score at study completion 90(+/- 7)
- Hospital Anxiety and Depression Score (HADS) at study completion 90(+/- 7)
- WPAI score at study completion 90 (+/- 7)
- VSAQ score at study completion 90 (+/- 7)
- COPD treatment adherence (what would be monitored and how would this be measured?)
- The number of exacerbations by study completion 90(+/- 7) days
- The time to exacerbations
- The rate of and timing of antibiotic use by study completion 90(+/- 7) days
- The rate of and timing of steroid use by study completion 90(+/- 7) days
- Safety the number of AEs and SAEs by study completion 90(+/- 7) days

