### **Work Productivity Activity Impairment (WPAI)**

The Work Productivity and Activity Impairment (WPAI) questionnaire is a well validated instrument to measure impairments in work and activities. The 6 questions relate to work absenteeism (hours missed work) Work presenteeism (impairment whilst working) and work productivity lost due to a health condition.

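### The printed WPAI form contradicts itself on attribution (COPD or any health problem), and for item 2 nothing resolves the conflict

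*Protocol*

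**What the plan says.** The outcome list under Intervention effectiveness outcomes includes the WPAI score at study completion. Appendix 1 schedules the questionnaire at Visit 1 and Visit 4. The protocol's description of the WPAI says that it "is a well validated instrument to measure impairments in work and activities" and refers to "work productivity lost due to a health condition", without saying whether that condition is COPD.

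The form itself is in Appendix 2. Its title gives the version as "General Health V2.0 (WPAI:GH", and its introduction states: "By health problems we mean any physical or emotional problem or symptom". Item 2 asks "how many hours did you miss from work because of your COPD", and its instruction then refers to absence because of health problems. Item 3 collects hours missed for any other reason. Items 5 and 6 ask about the effect of COPD on work productivity and on daily activities. Each has a restricting line before the scale; for item 6 it reads "Consider only how much COPD affected your ability to do your regular daily activities, other than work at a job". The 0-10 scale below that line starts at "Health problems had no effect on my daily activities", and item 5 follows the same pattern.

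**The concern.** A patient has to know whose burden to report: that of COPD alone, or that of all illness. The form gives both answers. The two readings can differ in this population. Co-morbidities are recorded (Clinical Data and PROMs), and the exclusion criteria remove only uncontrolled conditions judged to confound, so controlled co-morbidity stays in. Emotional problems fall within the form's own definition, and the trial measures anxiety and depression separately.

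The protocol specifies no primary outcome. Its stated objectives include describing the distributions of the effectiveness outcomes and choosing the primary outcome for the definitive trial, and the sample size rationale adds estimating the variance of the candidates. A score whose construct may vary from patient to patient serves those aims poorly.

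**Working it through.** The protocol gives no WPAI standard deviation, target difference or precision figure, so there is nothing to reproduce. The check is a comparison of the form's own wording, element by element.

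| Part of the form | Attribution |
|---|---|
| Title | General health |
| Definition in the introduction | Any health problem, physical or emotional |
| Item 2, question | COPD |
| Item 2, instruction | Health problems |
| Item 2, restricting line | None |
| Item 3 | Any other reason; other illness not mentioned |
| Items 5 and 6, question | COPD |
| Items 5 and 6, instruction | Health problems |
| Items 5 and 6, restricting line | COPD only |
| Items 5 and 6, both scale anchors | Health problems |

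All three impairment items (2, 5 and 6) carry both attributions. They differ in whether anything settles the matter:

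1. **Item 2.** Absence for a non-COPD illness belongs in item 2 by the instruction, but in item 3 by the question. No further line decides.
2. **Items 5 and 6.** The restricting line comes after the instruction and before the scale, and points to COPD. The anchors the patient then marks against point the other way.

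The consequence for item 2 can be shown with assumed hours, which are not from the protocol. Take a worker who misses 5 h for COPD and 5 h for another illness:

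- Following the question: item 2 = 5 h, item 3 = 5 h.
- Following the instruction: item 2 = 5 + 5 = 10 h, item 3 = 0 h.

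Total absence is 10 h either way, but item 2 doubles. In general the gap in item 2 equals the hours of non-COPD sickness absence, and it is zero when there is none.

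Reach also differs. Item 1 sends patients who are not employed straight to item 6, so items 2 to 5 are answered only by employed patients, and item 6 by everyone.

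**The case against.** The strongest case on the other side is that the fault is small. In items 5 and 6 the question and an explicit restricting line agree on COPD, so COPD is the dominant reading, and the leftover anchors may mislead few patients. Item 2, the only unresolved conflict, reaches only those in work. WPAI is also marginal here: the synopsis names it under procedures but not among the effectiveness outcomes, and Statistical Methods does not name it among the outcomes analysed by covariance adjustment. All of this stands, and it limits the weight of the point. It does not remove the contradiction, and an analysis plan cannot change what the patient reads on the page.

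Several stronger readings are tempting but not supported:

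- *That answers do measure different things in different patients.* The protocol shows only that they may, and only where another condition affected work or activity in the seven-day recall period.
- *That the definitive trial would need a stated percentage more patients.* Suppose a share p of patients answers for all illness and scores d points higher. The inflation is then 1 + p(1 - p)d²/SD². With SD 2.5, it is 1 + 0.09 × 1/6.25 = 1.01 for p = 0.1, d = 1, and 1 + 0.25 × 9/6.25 = 1.36 for p = 0.5, d = 3. Every input is hypothetical, p = 0.5 maximises the result, and the figure would matter only if this item became the primary outcome.
- *That the comparison between arms is biased.* Randomisation balances stable reading habits in expectation, and nothing in the protocol shows a difference by arm.
- *That the instrument's validation is lost.* The source cited for it is not at hand. What can be said is that the protocol does not show that its validation statement covers this mixed wording.

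**Conclusion.** The form is wrong as printed: its title, definition, questions, instructions and anchors do not agree on attribution. The conflict is unresolved in item 2 and partly resolved in favour of COPD in items 5 and 6. The likely result is added noise in a listed effectiveness outcome, confined to patients with other active conditions and, for item 2, to those who are also employed. For item 2 the discrepancy per patient equals the hours of non-COPD sickness absence. Its overall size cannot be derived, because the protocol gives neither the frequency of such absence nor any WPAI variance. The conclusion rests only on the printed wording and assumes that the Appendix 2 form is the one given to patients. It is a modest defect that is cheap to correct and worth correcting.

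**What to change.** Use one attribution throughout the form: title, definition, items 2, 5 and 6, their instructions and all scale anchors. Either COPD or general health would make it consistent. Name the chosen version in the outcome list under Intervention effectiveness outcomes and in the section describing the WPAI. The cost is one replacement appendix form, a line or two of protocol text and a check of the permissions for the wording used.

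Supplementary Table 1 reports no missing WPAI data at Month 0 or Month 3 in 41 participants, excluding the 6 who withdrew, so a WPAI form has evidently been completed. If it was this one, the report should say so and caveat the WPAI results, item 2 absenteeism in particular. The corrected form would then be for the definitive trial.
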